**2.4.1 Objective**

The objective of Phase 2 is to develop and content-validate a structured yoga module tailored to the physiological capabilities, safety requirements, and therapeutic needs of elderly adults with comorbid obesity and T2DM.

**2.4.2 Module development**

The yoga module will be developed through a systematic three-phase approach aligned with the Ministry of AYUSH, Government of India, guidelines.

**Step 1: Literature review**

A comprehensive review of traditional yogic texts including the Hatha Yoga Pradipika,
^
32
^ Gheranda Samhita,
^
33
^ Light on Yoga,
^
34
^ and Asana Pranayama Mudra Bandha
^
35
^ will be conducted alongside a structured search of contemporary scientific databases (PubMed, Scopus, Web of Science, Embase, and Ovid) using the key terms: yoga, elderly, type 2 diabetes, obesity, vascular health, brain, cognitive function, and neuroimaging. Studies reporting specific yoga practices with documented benefits for glycaemic control, vascular function, brain structure, or cognitive outcomes will be extracted and synthesized.

**Step 2: Integration and selection of practices**

Yoga practices identified as having therapeutic potential for vascular health, brain structural and functional improvement, and cognitive enhancement will be collated. These will be evaluated for their safety and practicability in the context of the target population’s physical limitations, comorbidities (osteoarthritis, reduced balance, cardiorespiratory deconditioning), and age-related contraindications to inversions, deep twists, and high-load postures. Selected practices will encompass asanas (physical postures), pranayama (breath regulation), and dharana/dhyana (mindfulness and concentration techniques).

**Step 3: Adaptation and manual preparation**

Selected practices will be adapted to accommodate the functional capacity of elderly obese-diabetic individuals. Modifications will include the use of props (chairs, bolsters, straps), reduced range-of-motion variants, seated and supine alternatives to standing postures, and graded progressions. A structured yoga manual will be produced, containing illustrated instructions, duration and frequency specifications, contraindication notices, and safety guidelines. The manual will be bilingual (English and Kannada) to ensure accessibility in the local population.

**2.4.3 Expert validation**

The completed yoga module will be submitted to a panel of eleven certified expert validators with recognized expertise in geriatric yoga, diabetes management, or integrative medicine. Validators will include yoga therapists, physiotherapists specializing in geriatric rehabilitation, endocrinologists, and exercise physiologists. Each expert will receive the module, along with a structured validation form and a written explanation of the study’s purpose and the validation process. Signed informed consent will be obtained prior to validation.

The validation form will assess each practice across three dimensions: usefulness, appropriateness, and relevance, rated on a 4-point Likert scale. The Content Validity Ratio (CVR) for each item will be calculated using Lawshe’s formula
^
36
^:

$$\mathrm{CVR}=\left(n_{e}-N/2\right)/\left(N/2\right)$$
where n
_e_ is the number of experts rating the item as ‘essential,’ and N is the total number of experts. Based on Lawshe’s table for 11 experts, a minimum CVR of 0.59 is required for an item to be retained (corresponding to agreement by ≥9 out of 10 experts) [39]. Items receiving agreement from fewer than 80% of experts will be reviewed, modified, or excluded based on expert commentary. The Content Validity Index (CVI) for the overall module will be computed as the mean CVR across all retained items.

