## 5 Discussion

The current protocol describes a comprehensive, three-phase investigation designed to characterize alterations in the vascular, structural, and functional brain networks associated with obesity and T2DM in elderly adults, and to evaluate the neuromodulatory potential of a validated, structured yoga intervention using multimodal MR neuroimaging. To our knowledge, this is the first study to employ a concurrent multi-sequence MRI protocol, encompassing T1-weighted VBM with CAT12 ROI segmentation, ExploreDTI-based white matter tractography, resting-state fMRI, and carotid Doppler ultrasonography, specifically in an elderly obese-diabetic population undergoing a structured yoga intervention.

The decision to adopt a three-phase sequential design reflects the complexity of the research question and the need to establish a robust methodological foundation before proceeding to the intervention. Phase 1 addresses the critical need for a detailed neurobiological characterization of the target population prior to any therapeutic application, providing both the baseline comparator data and the evidence base that informed the structure of the Phase 3 intervention. Phase 2 ensures that the yoga module delivered in Phase 3 is not only scientifically grounded but also culturally appropriate, practically feasible, and formally validated for safety and content, a step conspicuously absent in most existing yoga intervention trials, which have frequently relied on ad hoc or unstandardized practice regimens. Phase 3 then applies the validated module in a prospective pre-post design, enabling within-subject quantification of neuroplastic change across all imaging and cognitive domains characterized in Phase 1.

Several limitations of the present study design merit acknowledgment. The study population is drawn from a single tertiary hospital in coastal Karnataka, which may limit the generalisability of the findings to other regions of India and to populations with differing levels of yoga familiarity, dietary patterns, and genetic risk profiles for T2DM and obesity. Second, the 6-month intervention window, while among the longest in the yoga-neuroimaging literature, may be insufficient to detect macrostructural volumetric changes in highly atrophied regions; longer follow-up periods and multi-site designs should be incorporated in future work.

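### The Discussion credits Phase 2 with formal validation for safety and with feasibility, but the expert validation it describes has no criterion for either

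*Protocol article*

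**What the plan says.** Section 2.4.1 sets the aim of Phase 2 as to "develop and content-validate a structured yoga module tailored to the physiological capabilities, safety requirements, and therapeutic needs" of elderly adults with obesity and type 2 diabetes.

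Safety first appears in section 2.4.2. In Step 2, on the candidate practices: "These will be evaluated for their safety and practicability in the context of the target population’s physical limitations". Step 3 adapts the selected practices and produces a manual "containing illustrated instructions, duration and frequency specifications, contraindication notices, and safety guidelines".

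Formal validation follows in section 2.4.3, by "a panel of eleven certified expert validators". On what they rate: "The validation form will assess each practice across three dimensions: usefulness, appropriateness, and relevance, rated on a 4-point Likert scale". Retention uses Lawshe's CVR, where the count is of experts rating an item essential and the minimum is 0.59. Items with under 80% agreement are reconsidered in the light of the experts' comments. Section 2.4.4 describes the main output as a content-validated module.

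The Discussion (section 5) says that Phase 2 ensures a module that is "culturally appropriate, practically feasible, and formally validated for safety and content", and sets this against most existing yoga trials, which it says lack such a step.

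**The concern.** The Discussion claims two properties that the described validation does not measure. Section 2.4.3 names three dimensions and says that there are three. Safety is not among them, nor is feasibility, and the retention rule has no separate requirement for either. A high CVR would show that experts regard a practice as essential content. It would not show that they had been asked whether the practice is safe for this population.

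At stake is what Phase 2 may conclude. Participants are 60 to 80 years old, and Step 2 itself lists joint, balance and fitness limitations. The Discussion also foresees the validated module passing into community programmes and clinical guidelines if benefits are confirmed. A safety label attached in Phase 2 would travel with it.

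**Working it through.** **Claim and method side by side**

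| Property | Claimed in section 5 | Where Phase 2 addresses it | Scored, with a retention rule? |
|---|---|---|---|
| Content | Yes | Expert form and CVR, 2.4.3 | Yes |
| Safety | Yes, as formally validated | Step 2 evaluation; Step 3 adaptations, contraindication notices and safety guidance | No |
| Feasibility | Yes | Step 2 evaluation of practicability | No |

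For the Step 2 evaluation, no assessor, criterion or threshold is stated.

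**What the retention rule does with a minority safety objection**

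Inputs, all from section 2.4.3: N = 11 experts; CVR = (n_e − N/2)/(N/2); minimum CVR 0.59; review below 80% agreement.

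*The plan's own figure.* The article equates a CVR of 0.59 with at least 9 of 10 experts.
- N = 10: 8 endorsements give (8 − 5)/5 = 0.60, and 9 give (9 − 5)/5 = 0.80.
- N = 11: 9 endorsements give (9 − 5.5)/5.5 = 0.636.

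The stated equivalence is not reproduced: with 10 experts, 8 would already suffice. The count of 9 is right only with a denominator of 11. That mismatch is a separate point; N = 11 is used below.

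*Smallest passing count at N = 11.*
- CVR rule: n_e ≥ 5.5 + 0.59 × 5.5 = 8.745, so 9.
- 80% rule: n_e ≥ 0.80 × 11 = 8.8, so 9.

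| Endorse | Dissent | CVR | Agreement | Result |
|---|---|---|---|---|
| 10 | 1 | 0.818 | 90.9% | kept |
| 9 | 2 | 0.636 | 81.8% | kept, no review |
| 8 | 3 | 0.455 | 72.7% | fails, reviewed |

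Both rules give the same cut. If one or two of the 11 withhold endorsement because they consider a practice unsafe, it is kept and no review is triggered. Three or more such experts bring it to review.

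**The case against.** The strongest reply is that safety is handled, and that one clause in the Discussion is loosely worded. Much of this stands.

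- **Safety is considered before the panel.** Step 2 evaluates it against the population's limitations and age-related contraindications, and Step 3 adds modifications and safety guidance. A practice found unsafe there would be expected to drop out.
- **The panel is clinically qualified.** It includes geriatric physiotherapists, endocrinologists and exercise physiologists. Appropriateness is not defined in the article and may well cover safety in their minds.
- **Substantial dissent has an effect.** Three or more dissenting experts trigger review.
- **Objective, method and output agree.** Sections 2.4.1 and 2.4.4 promise content validation. The mention of safety requirements in 2.4.1 is an aim for tailoring the module.

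A reader might infer that a practice judged unsafe by any number of experts can be retained, or that safety is left to the module's developers alone. The documents support neither. The first inference assumes that clinicians would still endorse a practice they think hazardous. On the second, Step 2 does not say who evaluates safety. Nor does the long period of home practice measure this gap: it bears on the consequences, not on what the form asks. The article is also silent on whether modified items are rated again, which a condensed article may leave to the full protocol.

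The reply does not remove the discrepancy. The article counts and names the form's dimensions, so this is a stated content and not an omitted detail. An unscored selection step and manual text are not formal validation for safety.

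**Conclusion.** The point holds in limited form. Section 5 claims formal validation for safety, and feasibility, where the described Phase 2 delivers content validation. Under the stated rule, up to two of 11 experts may consider a practice unsafe and it is still kept without review.

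That figure rests on three assumptions: that the count of essential ratings and the 80% agreement refer to the same endorsements, that an expert who considers a practice unsafe withholds endorsement, and that all 11 experts rate each item. The article does not explain how 4-point ratings on three dimensions become a count of essential ratings. If experts take appropriateness to exclude safety, the rule defines no effect for a safety objection; if they take it to include safety, the two-dissenter margin applies.

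The documents do not show that the module would be unsafe, or that safety goes unexamined. They show that the claim exceeds the evidence Phase 2 is designed to produce.

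**What to change.** Reconcile sections 2.4.2 to 2.4.4 with section 5 in one of two ways.

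1. **Support the safety claim.** Add to the expert form a rated dimension for safety in this population, with its own retention requirement, so that an item is kept only if it also passes on safety. The cost is a slightly longer form and perhaps a few practices dropped. The article does not say whether the form has gone out; if it has, a short supplementary rating by the same panel would be needed.
2. **Limit the claim.** Reword section 5 to say that the module is content-validated. This costs one sentence.

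In either case, remove feasibility as a Phase 2 result, since Phase 2 describes no try-out in the target population. The 15-day in-person orientation cannot supply it, because it belongs to Phase 3 and comes after the module is validated.

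If practices are modified after review, it would be preferable to have the same panel rate the modified form. The content validity index is the mean CVR over retained items, and would then describe the version actually used. The cost is one short second round.

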**2.4.4 Outcomes**

The primary output of Phase 2 will be a content-validated, AYUSH-compliant, structured yoga module, accompanied by a bilingual participant manual, a facilitator guide, and a standardized session-delivery checklist. The validated module will serve as the basis for the Phase 3 intervention.

### 2.5 Phase 3

**2.5.1 Objective**

Phase 3 aims to investigate the effects of the validated structured yoga module on vascular health, structural and functional brain networks, and cognitive function in elderly adults with comorbid obesity and T2DM, using multimodal MR neuroimaging before and after a 6-month intervention period.

**2.5.2 Study design**

Pre-test post-test interventional study with repeated multimodal neuroimaging and cognitive assessment.

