**2.5.3 Participants**

Participants recruited in Phase 1 will be eligible for Phase 3. Inclusion and exclusion criteria will be reconfirmed at the time of enrolment into Phase 3. Participants who have developed new contraindications to yoga or MRI during the Phase 1 to Phase 3 interval will be excluded.

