**2.5.4 Intervention: delivery**

The structured yoga module validated in Phase 2 will be delivered to each participant as a printed bilingual manual accompanied by an illustrative video guide. An initial in-person orientation session (approximately 60 minutes for the first 15 days) will be conducted at CIMR, Manipal, during which a certified yoga instructor will demonstrate all practices, correct technique, and address safety questions.

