**2.5.10 Statistical analysis**

Pre- and post-intervention neuroimaging and cognitive outcomes will be compared using paired samples t-tests (or Wilcoxon signed-rank tests for non-normally distributed data). Mixed-effects linear regression models will be used to examine the longitudinal trajectory of outcome variables, adjusting for relevant covariates (age, sex, baseline physical activity, HbA1c, and medication use). The association between intervention-induced changes in neuroimaging metrics and changes in vascular, metabolic, and cognitive outcomes will be examined using partial correlations and multivariate regression. Effect sizes (Cohen’s d and partial η
^2^) will be reported for all primary outcomes.

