Notwithstanding these limitations, the present study addresses a genuinely underserved research priority. Elderly adults with obesity and T2DM represent one of the fastest-growing demographic segments in India and globally, yet they remain largely excluded from neuroimaging research and targeted yoga intervention trials alike. The multimodal, multi-phase design of this protocol, combining carotid vascular imaging, structural morphometry, white matter tractography, resting-state fMRI, and formal yoga module validation under a single framework, constitutes a methodologically rigorous and clinically meaningful contribution to the field. If the hypothesized neuroplastic and vascular benefits of structured yoga are confirmed, the validated module and accompanying evidence base generated by this study could be directly integrated into community-level NCD prevention programs, AYUSH clinical practice guidelines, and geriatric rehabilitation protocols across India.

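### Phase 3 is an uncontrolled before-after study, but the protocol words its result as an effect of yoga and does not list the missing control as a limitation; the pre-intervention scan may also predate yoga by an unstated interval

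*Protocol article*

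**What the plan says.** **Design and analysis.** Section 2.5.2 describes a "Pre-test post-test interventional study with repeated multimodal neuroimaging and cognitive assessment". Under section 2.5.4 the module "will be delivered to each participant as a printed bilingual manual accompanied by an illustrative video guide". Section 2.5.3 states that "Participants recruited in Phase 1 will be eligible for Phase 3", and no untreated, wait-list or randomised group is described anywhere. Section 2.5.10 says "Pre- and post-intervention neuroimaging and cognitive outcomes will be compared using paired samples t-tests", or by Wilcoxon signed-rank tests for non-normal data. It adds that "Mixed-effects linear regression models will be used to examine the longitudinal trajectory of outcome variables", adjusted for age, sex, baseline physical activity, HbA1c and medication use.

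**Timing.** Section 2.5.9 defines the primary outcomes as change from baseline, with 6 months given as the end point. Section 2.5.3 reconfirms eligibility at Phase 3 entry and says that people with new contraindications arising "during the Phase 1 to Phase 3 interval will be excluded". Section 2.5.8 schedules a full repeat of the Phase 1 battery after the intervention. The Discussion (section 5) calls the three phases sequential and describes Phase 1 as "providing both the baseline comparator data and the evidence base that informed the structure of the Phase 3 intervention".

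**Interpretation.** Section 2.5.10 labels the changes as induced by the intervention, and the abstract's background speaks of evaluating neuroplasticity induced by yoga. The Discussion looks ahead with "If the hypothesized neuroplastic and vascular benefits of structured yoga are confirmed, the validated module and accompanying evidence base generated by this study" and goes on to direct use in prevention programmes, clinical guidelines and rehabilitation protocols. The limitations it names are the single site and the 6-month window.

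**The concern.** A paired test asks whether the mean change differs from zero. When everyone is treated and there are two assessments, that mean is the sum of any yoga effect and everything else that changes between them. The protocol itself supplies rival explanations: participants are 60 to 80 years old, and the same Flanker and N-Back tasks are repeated.

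These push in different directions. Practice on the tasks would look like cognitive benefit. Ageing would lower brain volumes, so a real slowing of atrophy could appear as no change or as decline and be read as failure. Zero is not the change expected without yoga, so neither a significant nor a null result identifies the yoga effect.

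The baseline adds to this. If the Phase 1 scan is the pre-test, the period between scans is the gap plus 6 months, and drift during module development is counted in an outcome labelled as 6-month change.

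At stake is what may be claimed. As worded, a significant paired difference would count as confirmation and feed directly into guidelines.

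**Working it through.** **1. What the design can estimate.** Write the mean paired difference as D = Y + S, where Y is the yoga effect and S is all other change between the two assessments. Sections 2.5.2, 2.5.4 and 2.5.10 give one treated group and two assessments, so only D is estimable. Of the covariates in section 2.5.10, those fixed within a person (age at entry, sex, baseline activity) explain differences between people and do not split the within-person change into Y and S. HbA1c and medication use, if entered as time-varying, could account for part of S, but not for ageing or task practice, which run together with time since baseline.

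**2. Where the baseline lies.** Set side by side:
- Phase 1 contains the full battery (2.3.6).
- Module development and expert validation follow (2.4.2, 2.4.3), in a design called sequential (section 5).
- Phase 3 entry reconfirms eligibility only, and an interval is acknowledged but not quantified (2.5.3).
- The only imaging described within Phase 3 is the post-intervention repeat (2.5.8).
- The outcome is change from baseline to 6 months (2.5.9).

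Read together, these point to Phase 1 as the pre-test. This is an inference: the Phase 3 objective (2.5.1) speaks of imaging before and after the 6-month period, and nothing rules out a fresh scan at entry.

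**3. Illustration of size.** The article states no sample size for Phase 3, so there is no figure of its own to reproduce. Inputs:
- n = 40: an assumption, from the planned obese-diabetic group in 2.3.5.
- Two-sided 0.05: stated for Phase 1 in 2.3.6.7 and assumed to carry over.
- Y = 0.
- S in units of the SD of the change score, d: assumed.

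The paired statistic is then noncentral t with 39 degrees of freedom and noncentrality d√40. Probability of a significant result:

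| Non-yoga shift d | n = 40 | n = 80 (if both Phase 1 groups enter) |
|---|---|---|
| 0 | 5.0% | 5.0% |
| 0.1 | 9.5% | 14.3% |
| 0.2 | 23.5% | 42.4% |
| 0.3 | 45.7% | 75.5% |
| 0.4 | 69.4% | 94.2% |

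**4. Effect of a gap.** Assume linear drift and hold the SD of change fixed. The total shift is d₆ × (6 + gap)/6, where d₆ is the drift over 6 months. At n = 40:

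| d₆ | No gap | 6-month gap | 12-month gap |
|---|---|---|---|
| 0.1 | 9.5% (total 0.1) | 23.5% (0.2) | 45.7% (0.3) |
| 0.2 | 23.5% (0.2) | 69.4% (0.4) | 95.9% (0.6) |

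The gap lengths and drift values are assumptions.

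**5. What a concurrent control would cost in precision.** Assume a pre-post correlation of 0.9 and 80% power.
- Paired, n = 40: detectable shift 0.454 SD of change; SD of change = √(2 × (1 − 0.9)) = 0.447 baseline SD; 0.454 × 0.447 = about 0.20 baseline SD.
- Two arms of 20, ANCOVA on baseline: 0.909 × √(1 − 0.81) = about 0.40 baseline SD.

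The controlled comparison doubles the detectable difference. The paired figure, however, refers to D and not to Y.

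**The case against.** A single-arm before-after study is openly declared and is a legitimate first step. The wording is also more guarded than a hostile summary suggests: the Discussion sentence is conditional, integration is something that could follow, and the abstract says that findings will inform future randomised trials. The Introduction's complaint about causal inference is aimed at cross-sectional studies, and a longitudinal design does improve on those. The plan contains safeguards: one scanner, one sonographer, Flanker practice trials and covariate adjustment. Weekly contact and fitness tracking are parts of the delivered programme, not background drift. Practice effects touch only the cognitive outcomes, which are secondary.

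Most of this stands and limits the point, but none of it supplies the missing comparison. The conditional sentence still treats this paired test as what would confirm benefit, section 2.5.10 still calls the changes induced by the intervention, and the limitations still omit the control.

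Three stronger readings are tempting and are not supported:
- A reader might infer that the protocol already concludes that yoga works, or contradicts its own Introduction. It does neither outright.
- A reader might take it as stated fact that the pre-test is the Phase 1 scan. It is strongly implied, but no sentence says so, and an article may leave a visit schedule to the full protocol.
- A reader might take the percentages as rates of false yoga benefit. They rest on assumed drift and n, and for brain volumes the significant results would mostly show decline.

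**Conclusion.** The point holds as a mismatch between design and claim. Phase 3 can measure change over the period in which yoga is practised; it cannot attribute that change to yoga, and the covariates do not repair this. That follows from the stated design and needs no numerical assumption. The missing control belongs among the limitations and is absent.

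The timing point is secondary and rests on inference: the only pre-intervention battery described is Phase 1, and the interval to yoga is unstated. The main point stands even if there is no gap.

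The size is not known from the documents. Under the assumptions shown, drift of 0.1 to 0.4 SD of change at n = 40 moves the chance of a significant result from the nominal 5% to between 9.5% and 69.4%, in the direction of the drift. One might go further and say that Phase 3 is without value or must be randomised. The documents do not support that: its objective is framed as a before-and-after investigation, which the design can deliver if it is described as such.

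**What to change.** **Wording (needed).** Restate the Phase 3 objective and conclusions as uncontrolled, hypothesis-generating before-after change. Replace the terms that attribute change to yoga or to the intervention (abstract, 2.5.10) and the language of confirmation (section 5). Drop direct guideline integration as a consequence of this phase. Name the missing control as a main limitation. The cost is a weaker stated conclusion.

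**Baseline (needed).** Either state that the pre-intervention battery is the one taken shortly before yoga starts, or relabel the outcome as change from Phase 1 to post-intervention. The first can be arranged by scheduling Phase 2 before or alongside Phase 1 scanning. The Phase 2 steps draw on texts, literature and experts, but the Discussion says that Phase 1 informed the intervention, so that sentence must be reconciled first. In either case, enter the actual months between assessments in the mixed model. This makes the interval explicit; it does not replace a control. The cost is sequencing and a line in the analysis section. The article reports that no participant data had been collected at publication.

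**Optional, for the sponsor to weigh.** A randomised delayed start, with both groups reassessed before the delayed group begins, would give a concurrent comparison. With an assumed 20 per arm and correlation 0.9, the detectable difference is about 0.40 baseline SD, against about 0.20 for the paired test. It needs an amendment, delays yoga for half the participants, and adds about 20 batteries if the delayed group is also rescanned after yoga, as section 2.5.8 would require.
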